### Statistical Methods

The main purpose of this study is to compare the transfusion rate according to the implementation of patient blood management in patients with gynecologic cancer undergoing surgery. For other safety endpoints such as laboratory tests and vital signs, continuous data will be presented using descriptive statistics (ie, mean, SD, median, min, max) for each group, and categorical variables will be presented using frequency and percentage. If necessary, the Student t-test or Wilcoxon rank sum test will be performed for continuous data to test for differences in other safety endpoints between groups, and the χ^2^ test or Fisher’s exact test will be performed for categorical variables. Statistical analysis will be performed using IBM SPSS Statistics for Windows, Version 26.0 (IBM Corp, Armonk, New York, USA).

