**Major Inclusion/Exclusion Criteria:**

Patients who are diagnosed with gynecologic cancer (ie, endometrial cancer, cervical cancer, ovarian cancer) and scheduled for surgery will be included and their iron deficiency status will be assessed. Only those with a pre-operative hemoglobin level of 7 g/dL or higher will be included. Patients who underwent neoadjuvant chemotherapy or pre-operative radiation therapy will be excluded. Also, patients with serum ferritin >800 ng/mL or transferrin saturation >50% on serum iron panel tests will be excluded.

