## Introduction

Anemia is prevalent in cancer patients and affects 20–80% of patients with solid tumors.^1^ The causes of anemia in cancer patients include tumor-specific factors and treatment-related factors. Cancer-related chronic inflammation and cytokines can contribute to anemia by mediating the inhibition of erythropoietin production and iron sequestration.^2^ Acute bleeding from surgery, kidney failure due to chemotherapy, and bone marrow dysfunction due to chemotherapy and radiation or other treatments also contribute to cancer-related anemia.^3^ Most cases of anemia in cancer patients are iron deficiency anemia or anemia with functional iron deficiency.^4^ Anemia in cancer patients is associated with increased morbidity and mortality.^5 6^ Symptoms of anemia, which often manifest as shortness of breath, lethargy, palpitations, and fainting, can interfere with daily functioning and contribute to low quality of life.

Gynecologic cancer is associated with a high frequency of anemia (~85%). The frequency of anemia and blood transfusion is also reported to be very high during surgery, chemotherapy, and radiation therapy, which are the mainstay of treatment for gynecologic cancers.^7^ While the frequency of anemia before surgery ranges from 26% to 36%, the pre-operative and post-operative transfusion rates range from 41% to 77%.^8^ Previous studies have reported that anemia is associated with poorer outcomes for treatment and survival in gynecological cancers.^5 6^ Anemia is also associated with local tumor control failure, potentially related to treatment resistance by tumor hypoxia; accordingly, the hemoglobin level before treatment is a well-known prognostic factor of gynecologic malignancies.^5^ Therefore, the importance of anemia correction before treatment is increasingly emphasized in gynecologic oncology.

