### Sample Size

We performed sample size calculation through the Z-test with unpooled variance. Previous studies showed that the expected transfusion rate without patient blood management is 40%,^15 16^ and that the blood transfusion rate could be reduced by 25% through patient blood management. The following assumptions were made for calculating the required number of study participants: transfusion rate before, during, and after surgery when implementing patient blood management of 40%; level of significance α=0.05 (two-sided); and type II error, β=0.2 (ie, power=80%). The sample size was calculated using PASS version 15 (NCSS, Kaysville, Utah, USA) using the above settings and a total of 150 patients per group (total of 300 patients) were deemed necessary. Considering a dropout rate of 10%, we intend to enroll 167 patients per group (total 334 patients).

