### Randomization and Blinding

Patients will be randomly assigned in a 1:1 ratio to the patient blood management group and the conventional management group. A randomization table will be prepared using SAS software (SAS Institute, Cary, North Carolina, USA) by an independent statistician and study patients will be assigned using the stratified block randomization method. Stratification will be performed according to the type of cancer, International Federation of Gynecology and Obstetrics stage, and methods of surgery. Due to the nature of the study, blinding is not possible.

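### Adjusting the primary transfusion comparison for baseline haemoglobin and the randomisation strata would add modest precision at almost no cost

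*Protocol article*

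**What the plan says.** - **Statistical Methods (Protocol article).** Comparing the transfusion rate is called the main purpose, but no test is assigned to it. A t-test or Wilcoxon test is offered for continuous data, and a chi-square or Fisher's "exact test will be performed for categorical variables". These are to be used if needed, and for other safety endpoints.
- **Sample Size.** "We performed sample size calculation through the Z-test with unpooled variance". This is the only method the article links to the transfusion rate. It involves no covariates.
- **Randomization and Blinding.** "study patients will be assigned using the stratified block randomization method". The factors are cancer type, FIGO stage and surgical method; Hb is not among them. The trial is unblinded.
- **Step 1, both groups.** Patient blood management (PBM) patients receive intravenous iron before surgery at Hb 7–12 g/dL. On the day after surgery they receive it again at 7–12 g/dL, and red cells at 7 g/dL or less. Conventional patients receive one pack of red cells at 8–10 g/dL and two at 8 g/dL or less, both before surgery and on the day after.
- **Abstract, Major Inclusion/Exclusion Criteria.** "Only those with a pre-operative hemoglobin level of 7 g/dL or higher will be included". No upper Hb limit is given there or in the full inclusion criteria.

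**The concern.** The endpoint is transfusion, and Hb triggers transfusion by rule in both arms. Few baseline measurements could predict the outcome better. Two routine ways of using such a variable are stratifying the randomisation by it and adjusting the analysis for it. The article does not do the first and does not mention the second.

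Two things are at stake, and both concern precision. An analysis without baseline Hb leaves explainable variation in the treatment comparison and does not correct for chance imbalance in Hb between arms. An analysis that ignores the factors used in stratified randomisation overstates the standard error when those factors are prognostic, so the test is somewhat conservative.

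**Working it through.** **1. The plan's own figure.** Inputs from Sample Size: "level of significance α=0.05 (two-sided"), "type II error, β=0.2 (ie, power=80"%), and "the expected transfusion rate without patient blood management is 40"%. The comparison rate is taken as 25%, because that reading reproduces the stated number:

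n = (1.960 + 0.842)² × (0.40×0.60 + 0.25×0.75) / 0.15² = 7.849 × 0.4275 / 0.0225 = 149.13, so 150 per group. With 10% dropout, 150 / 0.90 = 166.7, so 167.

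A relative 25% reduction (40% vs 30%) would need 354 per group, so it is not the reading behind the plan's figure.

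Unadjusted power at 150 per group: SE = √(0.4275/150) = 0.0534; 0.15/0.0534 = 2.81; Φ(2.81 − 1.96) = 80.2%.

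**2. Gain from adjusting for baseline Hb.** The article gives no Hb–outcome association, so a range is assumed. For each odds ratio, 4,000 trials were simulated with 150 per arm and marginal rates of 40% and 25%. The adjusted analysis was a logistic model standardised to a risk difference, with influence-function variance.

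| Odds ratio per SD of Hb | Variance ratio, unadjusted/adjusted | Variance reduction | Power unadjusted | Power adjusted |
|---|---|---|---|---|
| 1.5 | 1.04 | about 3–4% | 81.2% | 82.1% |
| 2 | 1.10 | 9% | 78.4% | 81.9% |
| 2.5 | 1.15 | 13% | 80.2% | 86.0% |
| 3 | 1.20 | 17% | 79.5% | 86.9% |

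The reduction is 1 − 1/ratio; for example, 1 − 1/1.20 = 16.7%. The simulation error of each power is about √(0.8×0.2/4000) = 0.6 points. This explains why the unadjusted column scatters around 80%.

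**3. Cross-check by formula.** If Hb explains a share R² of outcome variance, power is Φ(2.81/√(1−R²) − 1.96). For R² = 5%, 10%, 20% and 30% this gives 82.2%, 84.2%, 88.1% and 91.9%. The simulated range corresponds to R² of roughly 3–17%, so the two methods agree. The last two values need a stronger association than the odds ratios above.

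**4. Chance imbalance in Hb.** Illustration only, using the Introduction: "While the frequency of anemia before surgery ranges from 26% to 36"%. With 150 per arm, the SD of the between-arm difference in prevalence f is √(2f(1−f)/150). That is 5.1 points at f = 0.26 and 5.5 points at f = 0.36. The chance of a difference above 10 points is then about 5% and 7%.

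**5. What a low-Hb subgroup could show.** If the same 26–36% had Hb of 12 g/dL or less, the subgroup would hold 150×0.26 = 39 to 150×0.36 = 54 patients per arm. Power for a 15-point difference (40% vs 25%) would be 30–39%.

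**6. Strata.** The precision lost by ignoring cancer type, stage and surgical method cannot be sized, because the article gives neither the number of levels nor their association with transfusion. Expected events are 150×0.40 + 150×0.25 = 97.5, so a model with every stratum cell could be sparse.

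**The case against.** The strongest objection is that the article does not fix an unadjusted primary analysis. The tests in Statistical Methods belong to safety endpoints, and the Z-test is a sizing formula. Covariates and subgroups are commonly left to the full protocol or the SAP, which are not at hand, so their absence is no error. An unadjusted randomised comparison is also valid, and the gain depends on assumed odds ratios; at the low end it is only about one point of power. All of this stands. It limits the point to a recommendation.

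A reader might infer three stronger things, none of which the documents support.

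- *That 64–74% of PBM patients will get no pre-operative iron.* This is 1 − 0.36 to 1 − 0.26. The Introduction offers 26–36% as a background rate, does not define anaemia and does not link it to the 12 g/dL threshold or to this trial's population. It also gives about 85% for anaemia in gynaecologic cancer generally.
- *That the planned effect needs a 42–58 point fall among iron recipients* (0.15/0.36 to 0.15/0.26). This holds only if pre-operative iron is the sole mechanism. PBM patients can also receive iron after surgery, and the arms transfuse at different Hb levels. A patient whose Hb falls to 9 g/dL after surgery is transfused by rule in one arm and not in the other, whatever the pre-operative value.
- *That the Hb 7–12 g/dL stratum would show whether pre-operative iron works.* Within that stratum the arms still differ in transfusion threshold and post-operative iron. The contrast is between whole strategies, and power is low for a 15-point effect.

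The stated objective covers iron before and after surgery as a programme, and a whole-group comparison does answer that question.

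**Conclusion.** The point holds as an efficiency recommendation. Baseline Hb sets treatment and drives the endpoint, is not a stratification factor, and is absent from the only method linked to the primary endpoint. Adjusting for it would reduce the variance of the risk difference by about 3–17% and lift power from about 80% to 82–87%. These figures assume odds ratios of 1.5–3 per SD, 150 evaluable patients per arm and true rates of 40% and 25%. Including the strata would also remove some conservatism, by an amount the article does not allow one to compute. The documents do not show an invalid analysis.

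**What to change.** State in the protocol or SAP, before outcome data are examined:

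1. **Primary analysis.** Transfusion within 3 weeks after surgery is analysed by a logistic model with arm, continuous baseline Hb and the randomisation strata. Use the Hb value measured before any study treatment. Report the standardised risk difference with 95% CI.
2. **Sparse strata.** Set in advance the rule by which small stratum cells are collapsed.
3. **Sensitivity analysis.** Keep the unadjusted two-proportion comparison, which matches the sizing.
4. **Results by baseline Hb** (12 g/dL or less versus above). Report each with its CI as supportive only, and read it as the effect of the whole strategy rather than of pre-operative iron.

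The cost is analysis wording. Pre-operative Hb is already needed for eligibility and the strata are already needed for randomisation, so no patients, visits or tests are added. The sample size need not change; the gain is best kept as a margin, since its size is assumed.

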## Discussion

Anemia in patients with cancer is associated with increased morbidity and mortality. Traditionally, blood transfusion has been performed to correct anemia in these patients, but transfusion has its own side effects and problems in blood supply have emerged recently. Therefore, many studies have been conducted to evaluate whether anemia can be effectively corrected using methods other than blood transfusion. In a phase III randomized study conducted at seven centers in South Korea, a placebo or ferric carboxy-maltose was administered to patients who had undergone extensive gastrectomy and had a hemoglobin of <7–10 g/dL after a few days of surgery.^13^ The hemoglobin levels were compared at 12 weeks after surgery and the results showed that the hemoglobin level was significantly higher in the iron supplement group by 2 g/dL or more.

However, there are no prospective studies that have evaluated the safety and efficacy of patient blood management for patients with gynecologic cancer undergoing surgery. Therefore, this trial is designed to demonstrate the safety and effectiveness of patient blood management in patients with gynecologic cancer undergoing surgery, adjuvant (chemo-)radiation therapy, and chemotherapy. In addition, there are no randomized controlled trials that have evaluated whether patient blood management can reduce the transfusion rate and improve surgical outcomes. This study will be the first randomized controlled trial to evaluate these issues. Through this study, we seek to provide evidence that patient blood management can effectively lower the transfusion rate of patients with gynecologic cancer. Since anemia and blood transfusion are associated with a poor survival prognosis in patients, developing a strategy to reduce transfusion during treatment would lead to improvements in the quality of treatment and increase the survival rate.^5^ In addition, the reduction in blood transfusion and transfusion complications can bring about economic effects through the reduction of medical costs and hospitalization. A reasonable and economical medical system can be established by enabling efficient pre- and post-surgery management. Furthermore, our results may pave the way to standardize blood management guidelines for patients with gynecologic cancer before, during, and after surgery and adjuvant treatment, and develop them as treatment guidelines.
